## Abstract

**Background:**

Despite advances in transplantation science, a persistent shortage of donor lungs continues to limit access to life-saving lung transplants. The Lung Donor (LUNDON) Acceptability Score is a validated tool that predicts donor lung utilization and post-transplant recipient outcomes, but integration into practice remains limited. This study will evaluate determinants of LUNDON score adoption, its impact on clinical decision-making, and develop tools to support its implementation.

**Methods:**

This is a multi-aim mixed-methods pre-implementation study that will be conducted across U.S. Organ Procurement Organizations (OPOs) and lung transplant centers. Aim 1 will identify barriers and facilitators of LUNDON score adoption through surveys (n = 242 participants) and interviews (n = 60 participants) of OPO and transplant providers. Aims 2 and 3 will evaluate the impact of the LUNDON score on donor management and organ acceptance using simulation-based experiments with OPO coordinators, OPO clinical leadership, transplant pulmonologists, and transplant surgeons (n = 120 total). Aim 4 will synthesize findings to develop and pilot implementation toolkits across three OPOs and three transplant centers. Two implementation frameworks [the Capability, Opportunity, and Motivation-Behavior (COM-B) model and the Theoretical Domains Framework (TDF)] will guide data collection and analysis, integrating quantitative and qualitative findings.

**Expected impact:**

Findings from this collaborative, nationally supported study involving partners from the United Network for Organ Sharing (UNOS) and the national lung transplant community will inform the development of toolkits to support LUNDON score adoption in clinical practice, with the goal of reducing variation in donor management and increasing donor lung utilization. Future studies will explore the effect of LUNDON score adoption on donor lung utilization and recipient outcomes.

## Introduction

Despite significant advances in transplantation science [1–3], a scarcity of donor organs limits access to life-saving transplants across the United States [4,5] and globally [1,6]. This gap is especially pronounced in lung transplantation [7–9], where stringent donor selection criteria [10] result in underutilization of potentially viable donor organs [11]. Despite recent advances in donor allocation reform [12], the national lung utilization rate (defined as the proportion of deceased donors whose lungs are ultimately transplanted) in 2024 was only 37% [13], which is markedly lower than for other organs (~66% kidneys; ~ 64% livers) [13]. A persistent shortage of donor lungs results in significant mortality on the lung transplantation waitlist [7,14]. Effort-intensive and costly approaches such as ex-vivo lung perfusion have not yielded a substantial increase in available donor lungs. Moreover, over 40% of donor lungs currently declined may actually be suitable for transplantation [15], perhaps attributable to wide variability in donor lung procurement and acceptance practices [16,17] leading to inequities [18–23] and missed opportunities for transplantation [9,24,25].

### Lung transplantation process

Lung transplantation is a complex, highly coordinated, multistep process involving multiple key constituent groups. After a patient with advanced lung disease is listed for transplantation, donor identification and assessment begin. Donors may be declared after brain death (DBD) or after controlled circulatory death (DCD). Donor suitability is assessed using standard or extended criteria [11,25], and then donors are actively managed to optimize organ function [11]. During this period, donor lungs are vulnerable to injury from ventilator-associated lung injury [11,26,27], aspiration and pulmonary infection [11,26], chest trauma related to the cause of death and/or resuscitation maneuvers [11], and fluid overload [26,28]. These vulnerabilities, combined with conservative acceptance thresholds, contribute to the low national lung utilization rate [29]. Donor lung evaluation requires integration of clinical data while balancing recipient factors and logistical considerations.

Organ procurement organizations (OPOs) coordinate donor evaluation, management, and organ allocation, thereby serving as the critical link between donor hospitals and transplant centers. Variation in donor management practices (e.g., ventilation parameters, diuresis, bronchoscopy, and treatment of infection) can substantially influence whether lungs are ultimately transplanted [17,30–34]. Following donor management, donor lungs are offered to a potential recipient on the waitlist according to established allocation policies that integrate disease severity, comorbidities, and predicted benefit of transplantation [7,11,35]. The potential recipient’s transplant team then decides whether to accept the offer, influenced by center-specific thresholds, provider experiences, and recipient acuity. Once donor lungs are allocated, a specialized procurement team retrieves and transports them to the recipient hospital, where the transplantation surgery is performed, completing the process from listing to implantation.

Transplant providers make several critical decisions along this pathway that directly influence organ utilization. They are often made under time substantial time constraints related to donor stability, organ allocation logistics, and recipient readiness. Given this inherent complexity and variability, adoption of standardized, data-driven tools is essential to promote consistent, evidence-based decision-making in donor evaluation and organ acceptance.

### Lung donor (LUNDON) acceptability score

To address the need for more standardized, evidence-based tools for lung donor evaluation, our group previously developed and validated the Lung Donor (LUNDON) Acceptability Score [33], a predictive model that estimates the likelihood of donor lung utilization based on nine clinically relevant variables (**Table 1**) and correlates with post-transplant recipient outcomes [34]. Using a large national cohort from the Scientific Registry of Transplant Recipients (SRTR), we derived and validated the model in over 80,000 brain-dead donors. The LUNDON score demonstrates excellent discrimination and calibration across diverse donor populations [36,37]. The score is operationalized as a user-friendly, web-based tool (https://sites.wustl.edu/lundon/) that provides real-time case-specific probability estimates and supports more objective and reproducible decision-making in donor evaluation and management.

**Table 1 pone.0342383.t001:** LUNDON score component variables.

NON-MODIFIABLE VARIABLES	POTENTIALLY MODIFIABLE VARIABLES *(with possible donor management strategies for improvement)*
**• Donor age in years** **• Smoking history >20 pack-years (yes/no/unsure)** **• History of myocardial infarction (yes/no/unsure)** **• Mechanism of death by asphyxiation or drowning (yes/no)** • **Cardiac arrest after brain death (yes/no)**	**• PaO2/FiO2 ratio** *Lung protective ventilation*^15^ *Lung recruitment maneuvers*^15^ *Prone positioning*^37^ *Bronchoscopy*^15^ **• Abnormal chest x-ray appearance (yes/no)** *Frequent bronchoscopy* *Lung recruitment maneuvers* **• Maximum creatinine (mg/dL)** *Goal-directed fluid resuscitation*^38^ *Avoidance of nephrotoxic medications* *Renal replacement when indicated*^39^ *Hemodynamic optimization*^38^ **• Bloodstream infection (yes/no)** Prevention: *Isolation precautions, hand hygiene, sterile protocol for central line management* [40] Treatment: *Antibiotics, identification and drainage of infection source when indicated*

Four of the nine component variables in the LUNDON score are potentially modifiable (**Table 1**), including (1) donor PaO2/FiO2 [P/F] ratio, (2) chest x-ray appearance, (3) creatinine, and (4) bloodstream infection. Prior work by our group has shown that lung-protective ventilation strategies and goal-directed donor management can improve oxygenation, radiographic findings, and renal function, corresponding with higher organ utilization rates [17,38,39,41]. These findings indicate that targeted, evidence-based interventions can improve LUNDON scores and expand the donor lung pool, providing actionable targets for OPOs to enhance donor management practices.

### Implementation gap

Despite strong validation across multiple studies, the LUNDON score remains underutilized in routine donor management and transplant decision-making. This reflects a broader and well-recognized phenomenon in medicine, where the translation of evidence-based innovations into routine practice is slow, inconsistent, and often incomplete [16,42,43]. Predictive tools such as the LUNDON score demonstrate excellent discrimination for donor lung utilization and post-transplant recipient outcomes, yet their integration into the time-sensitive, high-stakes clinical environment of transplantation remains limited.

Barriers to implementation of evidence-based practices in lung transplantation, such as the LUNDON score, may occur at multiple levels [44,45]. At the individual-level donor management decisions are frequently shaped by subjective judgment [46–49], institutional norms [46,50–52], and provider experience [46,50] rather than standardized data-driven approaches [11]. At the organizational level, variability in OPO workflows, limited interoperability of data systems, and the absence of embedded decision-support tools constrain adoption [8,53–55]. At the system level, the absence of structured implementation frameworks and performance feedback mechanisms perpetuates variation in donor evaluation and acceptance practices across centers [56,57].

Recent studies reinforce the need for deliberate implementation efforts. Our group and others have demonstrated that while the LUNDON score reliably predicts donor lung recovery and post-transplant recipient outcomes, its effectiveness depends on local calibration, consistent donor management strategies, and organizational readiness for change [34,36,37]. Collectively, these findings underscore that predictive validity alone is insufficient to drive behavioral change in the lung transplantation workflow.

### Implementation science

Implementation science is a field dedicated to promoting the adoption and sustained use of evidence-based practices [58] across diverse healthcare contexts through structured, multi-level frameworks and methods [59]. These frameworks help identify barriers and facilitators, develop targeted strategies, and evaluate mechanisms that drive behavioral and organizational change. Applying implementation science principles in the context of lung donor management [16,60] offers an opportunity to accelerate the integration of predictive models such as the LUNDON score into routine clinical practice.

### Expected impact

Grounded in implementation science methods, the proposed study aims to identify determinants (barriers and facilitators) of LUNDON score adoption in OPOs and lung transplant centers.

The integration of the LUNDON score into routine clinical practice has the potential to standardize donor evaluation, reduce unwarranted practice variation, and expand the pool of transplantable lungs. Ultimately, findings from this study will inform a future hybrid effectiveness–implementation trial designed to assess the real-world impact of LUNDON-guided donor management on organ utilization and recipient outcomes.

## Methods/Design

*Aims:*

**Aim 1**: Identify determinants (barriers and facilitators) of LUNDON score adoption.**Aim 2**: Evaluate the LUNDON score’s impact on donor management at OPOs.**Aim 3**: Evaluate the LUNDON score’s impact on donor lung acceptance decisions at lung transplant centers.**Aim 4**: Develop and pilot implementation toolkits to support national dissemination and uptake of the LUNDON score.

*Timeline:* The complete study timeline is provided in Fig 1. At the time of manuscript submission, participant recruitment has not yet been completed for any study aim, and no study results have been generated. Recruitment and data collection will proceed in staged phases as outlined in the study timeline (Fig 1). At the time of protocol submission, no study results were available.

**Fig 1 pone.0342383.g001:**
[figure not shown]
Study timeline and key activities.

Participant recruitment for Aim 1 is expected to begin on 01/02/2026 and continue through 30/06/2027. Recruitment for Aims 2 and 3 is expected to occur between 01/03/2027 and 31/12/2027. Recruitment for Aim 4 pilot testing is expected to occur between 01/09/2029 and 30/06/2030.

Based on the current study timeline, we estimate that participant recruitment will be completed by 30/06/2030 and data collection will be completed by 31/08/2030. As this is a multiple aim study with sequential phases, analyses and data dissemination will occur after completion of recruitment and data collection for each aim.We expect primary results beginning in 2027 and continuing through the end of the study period in 2030.

### Study design and setting

This is a pre-implementation study that will focus on U.S. OPOs and lung transplant centers, the key environments where donor evaluation and organ acceptance decisions occur.

### Study participants

Participants (**Table 2**) will include the following key constituent groups that are directly involved in donor evaluation and acceptance decisions: (1) OPO clinical leadership, (2) OPO donor coordinators, (3) transplant pulmonologists, and (4) transplant surgeons.

**Table 2 pone.0342383.t002:** Overview of target sample populations.

	AIM 1		AIM 2	AIM 3	AIM 4	
	Quantitative Phase	Qualitative Phase			Refinement Phase	Evaluation Phase
**Sample Population**	National sample from OPOs and LT centers	Purposive sample* of survey respondents	Purposive sample* of OPO personnel	Purposive sample* of LT providers	Key constituents from partner sites (3 OPOs, 3 lung transplant centers)	
**Sample Size**	N = 242	N = 60	N = 60	N = 60	N = 48	N = 12
**Participants**	OPO personnel (n = 112), LT providers (n = 130)	OPO personnel (n = 30), LT providers (n = 30)	CMOs (n = 30), Coordinators (n = 30)	Surgeons (n = 30), Pulmonologists (n = 30)	CMOs (n = 12), Coordinators (n = 12), Surgeons (n = 12), Pulmonologists (N = 12)	CMOs (n = 3), Coordinators (n = 3), Surgeons (n = 3), Pulmonologists (n = 3)
**Consent Process**	Implied by survey completion	Formal written	Implied by survey completion	Implied by survey completion	Formal written	Formal written

**Purposive sampling will ensure representation from low-, intermediate-, and high-performing organ procurement organizations (OPOs) and lung transplant (LT) centers (as defined by publicly reported lung utilization rates and organ acceptance rates, respectively).*

These multidisciplinary groups represent the primary potential end-users of the LUNDON score and are integral to understanding contextual barriers and facilitators to its adoption. Participants will be identified through the professional networks of the study team and invited with support from the study’s advisory board to ensure broad representation across institutions and geographic regions.

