### Sample size determination and sampling strategy

Sample sizes for each aim are detailed below. Sampling strategies were informed by our team’s prior unpublished work within the relatively small, close-knit community of OPOs and lung transplant clinicians. Based these experiences, we anticipate response rates exceeding 70%. Sample size estimates account for this expected level of participation.

To evaluate and minimize potential non-response bias, an interim analysis will be conducted after 40% of the survey samples have been enrolled for Aims 1–3. Key demographic and professional characteristics of responders and non-responders will be compared. If systematic differences are observed, targeted oversampling will be employed to ensure representation of participants with characteristics similar to non-responders for the remainder of enrollment.

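### The Aim 1 survey is called national but invitees come from the score developers' networks; this risks coverage bias of unknown size that the planned non-response check cannot detect

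*Protocol article*

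**What the plan says.** In the Protocol article, Table 2 (Study participants) labels the Aim 1 quantitative phase a "National sample from OPOs and LT centers", with 112 OPO personnel and 130 lung transplant providers. The text under the table gives the route into the study for participants generally: "Participants will be identified through the professional networks of the study team". The same sentence adds that they are "invited with support from the study’s advisory board to ensure broad representation across institutions and geographic regions".

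The section on the LUNDON score states that "our group previously developed and validated the Lung Donor (LUNDON) Acceptability Score", so the networks in question are those of the developers.

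The section on sample size and sampling strategy describes the field as a "relatively small, close-knit community of OPOs and lung transplant clinicians" and expects response above 70%. Its safeguard is an interim look after 40% of the survey samples are enrolled: "Key demographic and professional characteristics of responders and non-responders will be compared". If the groups differ, people resembling the non-responders are oversampled for the rest of enrolment.

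Sampling by site performance tier is stated for the Aim 1 interviews and for Aims 2 and 3. It is not stated for the Aim 1 survey.

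**The concern.** The label and the identification method do not match. A national sample implies a frame that covers the country's OPOs and lung transplant centers. The method described reaches those whom the team already knows or can find through its contacts.

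The mismatch matters because of what Aim 1 measures. After an educational video, respondents report their interest in adopting the score, and the aim is to find barriers to and facilitators of adoption. People connected to the developers may plausibly know the score better and view it more favourably. Unconnected or sceptical users, whose barriers are the most informative, are the ones such a frame is most likely to miss. The likely direction of error is therefore interest too high and barriers too few.

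The interviews do not provide an independent view, because they are drawn from survey respondents and inherit the same frame. Aim 4 then builds toolkits meant for national uptake partly on these results.

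**Working it through.** **1. The protocol's own figures.** 112 + 130 = 242, which agrees with Table 2. The article derives this number from no precision or power target, so there is nothing further to reproduce.

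**2. What the interim check can see.** Take 242 as completed surveys and a 70% response.
- Responders at the 40% trigger: 0.40 × 242 = 96.8, about 97.
- Invited by then: 96.8 / 0.70 = 138.3.
- Non-responders: 138.3 × 0.30 = 41.5, about 41.

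All of these people, about 138, were invited. Anyone the network never identified is in neither group, so the comparison carries no information about them. The variables compared are demographic and professional; closeness to the team and prior exposure to the score are not named. Oversampling people who resemble non-responders does not by itself extend the frame.

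**3. How large the bias could be.** Let c be the share of the target community that the network reaches, and d the difference in interest between people inside and outside it. Then

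bias = (1 − c) × d.

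Neither c nor d is in the documents, so both are assumed here. Also assume 70% interest inside the network and simple binomial sampling with n = 242:

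SE = √(0.70 × 0.30 / 242) = 0.0295; 95% half-width = 1.96 × 0.0295 = 5.8 points.

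Actual coverage of a nominal 95% interval = Φ(1.96 − bias/SE) − Φ(−1.96 − bias/SE).

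| Network reach c | Gap d (points) | Bias (points) | Actual coverage |
|---|---|---|---|
| any | 0 | 0 | 95% |
| 95% | 20 | 1 | 94% |
| 80% | 10 | 2 | 90% |
| 80% | 20 | 4 | 73% |
| 80% | 30 | 6 | 47% |
| 60% | 10 | 4 | 73% |
| 60% | 20 | 8 | 23% |
| 60% | 30 | 12 | 2% |

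The bias runs from nothing to about twice the sampling half-width (12 / 5.8 = 2.1). As described, the study would collect nothing that shows where in this range it lies.

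**The case against.** Five points can fairly be made on the other side.

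- **There is a stated safeguard.** The identification sentence goes on to promise advisory-board support for breadth across institutions and regions. This is real but partial. It can widen the geography. It is not an independent frame, and it does not address affinity to the score.
- **The field is small.** In a close-knit community, with UNOS, OPO and transplant partners on the study, the network may reach nearly every site. This stands: at 95% reach even a 20-point gap costs only 1 point. A reader might infer from the mismatch that the results are biased. The documents do not support that, since they give neither the reach nor any gap in attitude.
- **Aim 1 is not a prevalence survey.** It is a mixed-methods search for determinants, sized by information power, with no confidence interval stated. This also stands, and interval coverage above is only a yardstick. Still, finding which barriers exist depends on the range of people reached, and that is what the frame limits.
- **An article condenses.** Details of a contact list may sit in the full protocol. The article does, however, state an identification method, and that method does not fit the label beside it.
- **Aims 2 to 4.** A reader might infer that the same people carry through the whole study. Only the interviews draw on survey respondents. Aims 2 and 3 use their own purposive samples across performance tiers, with randomised score visibility and within-subject comparison, so closeness to the team would there mainly limit generalisability. Aim 4 recruits at partner sites.

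**Conclusion.** The concern holds as a risk of coverage bias, of unknown size, in the Aim 1 survey and in the interviews drawn from it. Three things are established from the text: a sample labelled national is identified through the developers' networks; the planned check covers only invited people and cannot detect under-coverage; and no performance strata are stated for the survey.

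The direction (interest overstated, barriers understated) is plausible but not shown. The size depends wholly on assumed values: 1 point of bias at 95% reach with a 20-point gap, 4 points at 80%, 8 points at 60%, and none without a gap. No sample-size or power error is involved, and the study is not invalidated. The change is a cheap improvement that would make the problem either avoidable or measurable.

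**What to change.** 1. Build the Aim 1 invitation list from the full list of U.S. OPOs and active lung transplant centers. This should be obtainable through the UNOS partner. Use the team's networks and the advisory board to endorse invitations and send reminders.
2. Extend the interim comparison to represented versus unrepresented sites, using the publicly reported utilization and acceptance rates already planned for tiering, and direct the oversampling to unrepresented sites.
3. Ask each respondent about prior familiarity with the score and ties to the study team. Put these items with the demographic questions, before the educational video, and report interest and barriers by them.
4. If the network frame is kept, describe the sample as network-identified rather than national.

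The cost is one list request to an existing partner, a few survey items and some contact work at less familiar sites. Response may fall below the anticipated 70%, which exchanges some coverage error for non-response. Non-response is at least visible to the planned check. If sites are asked to name their role-holders, that brings some selection of its own and should be reported.
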